## Abstract

**Background:**

Head injury is an extremely common clinical presentation to hospital emergency departments (EDs). Ninety-five percent of patients present with an initial Glasgow Coma Scale (GCS) score of 13–15, indicating a normal or near-normal conscious level. In this group, around 7% of patients have brain injuries identified by CT imaging but only 1% of patients have life-threatening brain injuries. It is unclear which brain injuries are clinically significant, so all patients with brain injuries identified by CT imaging are admitted for monitoring. If risk could be accurately determined in this group, admissions for low-risk patients could be avoided and resources could be focused on those with greater need.

This study aims to (a) estimate the proportion of GCS13–15 patients with traumatic brain injury identified by CT imaging admitted to hospital who clinically deteriorate and (b) develop a prognostic model highly sensitive to clinical deterioration which could help inform discharge decision making in the ED.

**Methods:**

A retrospective case note review of 2000 patients with an initial GCS13–15 and traumatic brain injury identified by CT imaging (2007–2017) will be completed in two English major trauma centres. The prevalence of clinically significant deterioration including death, neurosurgery, intubation, seizures or drop in GCS by more than 1 point will be estimated. Candidate prognostic factors have been identified in a previous systematic review. Multivariable logistic regression will be used to derive a prognostic model, and its sensitivity and specificity to the outcome of deterioration will be explored.

**Discussion:**

This study will potentially derive a statistical model that predicts clinically relevant deterioration and could be used to develop a clinical risk tool guiding the need for hospital admission in this group.

## Background

There are 1.4 million annual attendances to emergency departments in England and Wales following a head injury [1]. Approximately 95% of patients present with an initial score of 13–15 on the Glasgow Coma Scale (indicating a normal or mildly impaired conscious level) and are defined as having a “minor head injury”[2]. Minor head injured patients have a 1% risk of life-threatening traumatic brain injury (TBI) [3]. In the UK, head injury guidelines are used to triage CT imaging in this large patient population with the aim of identifying all life-threatening injuries [1, 4]. Adult guidelines are based on the internationally used and validated Canadian CT Head Rule and are applied to patients aged ≥ 16 [3, 5]. Around 7% of patients have TBI identified by CT imaging [6]. All of these patients are admitted to hospital in the UK due to fears about the risk of deterioration due primarily to intra-cranial haematoma progression, but these risks are not well characterised (Fig. 1).

**Fig. 1 Fig1:**
[figure not shown]
Current management of minor head injured patients

The management of GCS13–15 patients with CT-identified TBI is controversial with some advocating admission to higher levels of care and mandatory repeat CT imaging due to the risk of deterioration [7]. Others argue that some patients are at low enough risk to be discharged safely from the ED after a short period of observation, a model of care adopted in a level 1 trauma centre in Arizona [8]. The UK NICE guidelines (published 2004, 2007 and 2014) state that all patients with significant brain injuries identified by CT imaging should be admitted to hospital, but do not qualify what constitutes such injuries [1].

In our recent systematic review, we estimated a pooled risk of neurosurgery in GCS13–15 patients with injuries identified by CT imaging of 3.5% (95% C.I. 2.2–4.9%) from the results of 36 studies [9]. A risk of clinical deterioration, such that patients would benefit from inpatient hospital admission, of 11.7% (95% C.I 11.7–15.8%) was derived from 18 studies. There was significant variation in estimates of these outcomes across individual studies, and no studies were conducted in the UK where NICE guidelines are used, so relevant risk factors were not considered. Following the introduction of the NICE guidelines, hospital admissions for head injury increased in England [10]. It is thought this may be due to more injuries of less clinical significance being identified due to increased CT imaging of minor head injured patients [10]. Research is required to estimate the risks of adverse outcomes in GCS13–15 patients with injuries identified by CT imaging in the UK.

GCS13–15 patients with brain injuries identified by CT imaging have a small but clinically important risk of significant adverse outcomes. Well-conducted prognostic research could generate models which allow the identification of low-risk patients who could be safely discharged from ED and high-risk patients who would benefit from more aggressive management. Our review identified 41 factors in 21 studies that had been assessed as potentially affecting the risk of adverse outcomes in this group [9]. None of this research was conducted in the UK, and no multivariable models were identified that could be used to accurately identify patients at sufficiently low risk of deterioration to be discharged from the ED. Prognostic research conducted within the context of NHS care is required to assess the extent to which GCD13–15 patients with CT-identified TBI can be stratified by risk. This will help refine the NICE guidelines and potentially allow better resource allocation in the management of these patients by identifying those who do not require hospital admission.

### Aims

Estimate the prevalence of clinical deterioration in initial GCS13–15 adult patients with brain injuries identified by CT imaging.Develop a multivariable model that accurately identifies adult patients at sufficiently low risk of clinical deterioration that they could be discharged from the ED.

## Methods

### Study design

This is a retrospective and consecutive cohort observational study. The proportion of the cohort that clinically deteriorates will be estimated, and a multivariable prognostic model that predicts deterioration will be developed. The study will be conducted and reported in accordance with the Transparent Reporting of a multivariable prediction model for Individual Prognosis or Diagnosis (TRIPOD) recommendations [11, 12].

Patients will be identified through a retrospective case note review over a 10-year period from the end of 2007 to 2017 at Hull Royal Infirmary and Salford Royal Hospital, two English major trauma centres.

### Participants

#### Inclusion criteria

The inclusion criteria include patients aged ≥ 16 admitted to hospital, with an initial GCS of 13 or more on presentation to the ED and traumatic brain injury identified definitively by CT head imaging. All patients with epidural haemorrhage, subdural haemorrhage, subarachnoid haemorrhage, intra-cerebral haemorrhage, intra-cerebral contusion, skull fractures and any combination of these injuries will be considered for inclusion. All patients with injuries identified by CT that could only be traumatic in aetiology including skull fractures, extradural haemorrhages and subdural haemorrhages will be counted as having traumatic brain injury. Where patients have intra-cranial haemorrhage identified that could be either traumatic or spontaneous, patients will only be included if they have either a documented mechanism or evidence of head injury. This will apply to intra-cerebral and subarachnoid haemorrhages. Included mechanisms are falls, assault, road traffic collision, sport and any other mechanism that could result in blunt trauma above the clavicles. Evidence of head trauma includes bruising, wounds or injuries above the clavicles including facial and skull fractures identified radiologically.

#### Exclusion criteria

Exclusion criteria include patients with obvious penetrating head injury or with spontaneous intra-cranial haemorrhage. Patients will be categorised as having a spontaneous intra-cranial haemorrhage if the haemorrhage could occur spontaneously or traumatically and they have no documented preceding mechanism or evidence of head injury or if the CT report states that the pattern of intra-cranial haemorrhage indicates a spontaneous event. Patients with pre-existing brain injuries or other pathology that makes the interpretation of timing of injury difficult are excluded, and this includes patients with haemorrhagic brain tumours, chronic subdural haemorrhage or hygromas and other types of pre-existing intra-cranial bleeds. Patients with isolated occipital condyle fractures are excluded as these are treated as cervical spine injuries. Patients transferred from other EDs following identification of a brain injury will also be excluded.

### Study outcome

The outcome of interest is a composite measure of clinical deterioration such that inpatient hospital admission was warranted; this includes death due to TBI or neurosurgery within 30 days of attendance, ICU intervention whilst an inpatient, seizure activity whilst an inpatient, drop in GCS by 2 or more points whilst an inpatient or a readmission to hospital within 30 days of injury related to TBI.

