### Candidate prognostic factors

Potential candidate factors have been selected a priori by identification of factors that individually predict deterioration in the study population in our systematic review, inclusion of additional factors that predict adverse outcomes in prognostic models for patients with more severe TBI and trauma and inclusion of factors that represent NICE guideline standards and criteria for treatment and investigation of head injury and TBI [1, 9, 13–15]. All factors being considered for inclusion in the final model are presented in Table 1 with the reason for their inclusion.

**Table 1 Tab1:** Prognostic factors being investigated

Factors from systematic review	Type of data	Factors from NICE guidelines	Type of data	Factors from TARN TBI/trauma model	Type of data
Age	Continuous	1st neurological examination in ED	Categorical	Admission Hb	Continuous
Sex	Categorical	Equal pupils 1st examination	Categorical	Admission platelets	Continuous
Pre-injury anti-coagulant use	Categorical	Both pupils reactive 1st examination	Categorical	Charlson Trauma Modified Comorbidity Index	Continuous
Pre-injury anti-platelet use	Categorical	SIGN of skull fracture 1st examination	Categorical	Admission BM	Continuous
GCS on arrival to ED	Categorical	Seizures in ED	Categorical	Frailty score	Continuous
BP on arrival ED	Continuous	Vomiting in ED	Categorical		
HAIS	Continuous	An occupant ejected from a motor vehicle	Categorical		
Marshall Classification	Categorical	Mechanism of injury	Categorical		
Single injury	Categorical	Amnesia	Categorical		
Comment on midline shift	Categorical	Intoxicated EToH time of injury	Categorical		
Comment on size of bleed		Seizures before arrival ED	Categorical		
Additional injuries	Categorical	Vomiting before arrival ED	Categorical		
Sats on arrival ED	Continuous	A pedestrian or cyclist struck by a motor vehicle	Categorical		
		A fall from height of > 1 m or 5 stairs	Categorical		

Comorbidities will be measured using a trauma-modified Charlson Comorbidity Index. Brain injury severity, as shown on CT scan, will be stratified using the Marshall Classification, which will be calculated from Abbreviated Injury Severity (AIS) codes for TBI using the method described by Lesko et al. [16, 17] The Charlson Comorbidity Index, AIS and Marshall Classification are internationally validated prognostic scoring systems [18, 19]. Frailty will be assessed using the clinical frailty scale described by Rockwood et al. [20].

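### The composite outcome and the candidate predictors share no prediction time, so model accuracy is measured partly off the ED discharge decision

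*Protocol article*

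**What the plan says.** Under Aims, the model is to find adults "at sufficiently low risk of clinical deterioration that they could be discharged from the ED". The Background describes the competing model of care as patients being "discharged safely from the ED after a short period of observation". Under Model accuracy, the target is a 1/100 risk after discharge, pursued through at least 99% sensitivity. All three point to a decision taken once the CT has been read and the patient has spent some time in the ED.

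The Study outcome section uses three clocks:

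- From attendance: "death due to TBI or neurosurgery within 30 days of attendance".
- While an inpatient: "ICU intervention whilst an inpatient, seizure activity whilst an inpatient", and "drop in GCS by 2 or more points whilst an inpatient".
- From injury: "a readmission to hospital within 30 days of injury related to TBI".

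The start of inpatient status and the reference value for the GCS drop are not stated. Entry rests on GCS at presentation. Nothing in the inclusion or exclusion criteria removes a patient who goes from the ED to theatre. In Table 1, GCS appears only as "GCS on arrival to ED", next to the first neurological examination. Seizures and vomiting in the ED are also candidate factors, so the predictor window does run past arrival for some items.

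Under Model accuracy, the model is also to be derived again in patients who have not deteriorated by 24 h.

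**The concern.** A model for a discharge decision should use what is known when that decision is made and be scored on what happens afterwards. Here the two sides do not meet at one time.

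- **Surgery decided in the ED.** The patient is admitted, so is in the cohort, and has surgery within 30 days of attendance, so is an event. Table 1 includes Marshall class, head AIS, midline shift and bleed size, which are likely to pick this patient out. The model is credited with a correct prediction for someone who was not a candidate for discharge.
- **GCS fall in the ED.** Take a patient who arrives at 15, falls to 13 in the ED and stays at 13 on the ward. If the inpatient drop is measured from ward entry, the patient is a non-event with a recorded GCS of 15. If it is measured from arrival, the patient is a later event that had already happened. Under neither reading does a predictor carry the fall.

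For seizures the plan draws the line properly: those in the ED are predictors and those on the ward are outcomes. GCS and neurosurgery have no such separation. What is at stake is how well the reported sensitivity, specificity and C-statistic describe the patients a clinician might send home.

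**Working it through.** **The plan's own figures first.** Inputs from Sample size: target sensitivity 0.99, margin 0.014, prevalence 10%, about 2000 patients.

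- Events needed = 1.96² × 0.99 × 0.01 / 0.014² = 194.0.
- N = 194.0 / 0.10 = 1940, which agrees with about 2000.
- Margin at 200 events = 1.96 × √(0.99 × 0.01 / 200) = 1.38%.
- Prevalence margin = 1.96 × √(0.10 × 0.90 / 2000) = 1.31%, against the 1.3% given under Outcome estimate.

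**Events that could precede the decision.** The Background gives pooled neurosurgery risk as 3.5% (95% CI 2.2–4.9%). In 2000 patients that is 70 (44 to 98), out of 0.10 × 2000 = 200 planned events. The article does not give the share of surgery decided in the ED. I assume 10–50%, and assume that each such patient has no other qualifying event.

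Suppose the model misses 2 of 200 events (reported sensitivity 198/200 = 99.0%) and flags every ED-surgery patient as high risk. Both misses then fall among the later events. Sensitivity in those events is 1 − 2/E, and the margin is 1.96 × √(0.0099/E), where E is the number of events after the decision.

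| Share decided in ED | Events before decision | E | Sensitivity in later events | Overstatement | Margin |
|---|---|---|---|---|---|
| 0% | 0 | 200 | 99.00% | 0 | 1.38% |
| 10% | 7 (3.5% of 200) | 193 | 98.96% | 0.04 points | 1.40% |
| 25% | 17.5 (8.75%) | 182.5 | 98.90% | 0.10 points | 1.44% |
| 50% | 35 (17.5%) | 165 | 98.79% | 0.21 points | 1.52% |

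The planned 1.4% margin needs 194.0 events, so it is passed once more than about 6 of the 200 are removed.

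**What cannot be sized.** The article gives no count of GCS falls in the ED, no timing of surgery or ICU intervention, and no expected C-statistic. Any figure for the C-statistic, the specificity or the number of ED GCS falls would be invented.

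**Does another passage close the gap?** The Abstract lists a GCS drop of more than 1 point without a window, which settles nothing. If inpatient status were taken to begin at ED arrival, the GCS gap would close, but seizures in the ED would then be both predictor and outcome.

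**The case against.** The strongest reply is that the breadth is intended. The composite is meant to capture deterioration that warranted admission, and the Strengths section says it was drawn widely to reflect the benefits of admission. A patient who needs surgery on the index CT did warrant admission, so scoring that patient positive fits an admit-or-discharge split. This stands for Aim 1. It does not show how the model performs in patients for whom discharge was still open.

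Second, patients operated on from the ED within 24 h drop out of the 24 h re-derivation, so they cannot flatter that model. This stands in part. But 24 h is a later landmark: it also discards events between ED disposition and 24 h, which a discharge tool has to catch.

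Third, a journal article may leave extraction definitions, such as the reference GCS, to the full protocol. That is fair for the baseline of the drop. It does not cover the attendance clock for neurosurgery or the GCS entry in Table 1, both of which the article states.

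Stronger readings are tempting but not supported:

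- *That the prevalence is inflated.* Aim 1 concerns all adults with initial GCS 13–15 and CT-identified injury, so surgical cases belong in it. Removing 35 gives 165/1965 = 8.4% and removing 17.5 gives 182.5/1982.5 = 9.2%, but these describe a different population. Only the first differs from 10% by more than the 1.3-point margin.
- *That the C-statistic is materially inflated.* The article offers no value from which to show it.
- *That the model is not tested on its decision at all.* Many events probably occur after admission and remain informative.

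**Conclusion.** The point holds as a partial misalignment. The composite and Table 1 have no common prediction time. Surgery decided in the ED counts as predicted deterioration, and a GCS fall in the ED is recorded nowhere in the model. The 24 h re-derivation repairs this only in part, and the Aim 1 prevalence is not affected.

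The likely effect on the headline target is small. With the pooled 3.5% neurosurgery risk and an assumed 10–50% decided in the ED, 7–35 of 200 events precede the decision, sensitivity is overstated by about 0.04–0.2 points, and its margin becomes 1.40–1.52%. These figures also assume that the ED-surgery patients have no other qualifying event and are all flagged by the model. They mix a neurosurgery risk pooled from 36 studies with a planning prevalence of 10%. The GCS part rests on the text alone and cannot be sized. The case for change is that it is cheap and that an ED GCS never extracted cannot be recovered at analysis.

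**What to change.** 1. State one prediction time: ED disposition after the CT report.
2. Extract the last ED GCS before disposition in addition to arrival GCS, as a candidate factor and as the baseline for the inpatient drop. Arrival GCS should stay: it comes from the systematic review, and Table 2 shows it is available in the Italian data.
3. Flag patients whose neurosurgery, ICU intervention or GCS drop of 2 or more points was decided or occurred before disposition.
4. Keep flagged patients in the Aim 1 prevalence and show their share separately.
5. Report the C-statistic, sensitivity and specificity both for all patients and with flagged patients excluded.

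The cost is one GCS value and one timing flag per patient from case records already being read. Some last-ED GCS values will be missing and would go into the planned multiple imputation. The restricted analysis has fewer events: at 165, the plan's rule of 10 events per parameter allows about 16 parameters rather than 20, and the sensitivity margin rises to about 1.5%. The all-patient analysis keeps the planned precision.

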### Candidate prognostic factors

Potential candidate factors have been selected a priori by identification of factors that individually predict deterioration in the study population in our systematic review, inclusion of additional factors that predict adverse outcomes in prognostic models for patients with more severe TBI and trauma and inclusion of factors that represent NICE guideline standards and criteria for treatment and investigation of head injury and TBI [1, 9, 13–15]. All factors being considered for inclusion in the final model are presented in Table 1 with the reason for their inclusion.

**Table 1 Tab1:** Prognostic factors being investigated

Factors from systematic review	Type of data	Factors from NICE guidelines	Type of data	Factors from TARN TBI/trauma model	Type of data
Age	Continuous	1st neurological examination in ED	Categorical	Admission Hb	Continuous
Sex	Categorical	Equal pupils 1st examination	Categorical	Admission platelets	Continuous
Pre-injury anti-coagulant use	Categorical	Both pupils reactive 1st examination	Categorical	Charlson Trauma Modified Comorbidity Index	Continuous
Pre-injury anti-platelet use	Categorical	SIGN of skull fracture 1st examination	Categorical	Admission BM	Continuous
GCS on arrival to ED	Categorical	Seizures in ED	Categorical	Frailty score	Continuous
BP on arrival ED	Continuous	Vomiting in ED	Categorical		
HAIS	Continuous	An occupant ejected from a motor vehicle	Categorical		
Marshall Classification	Categorical	Mechanism of injury	Categorical		
Single injury	Categorical	Amnesia	Categorical		
Comment on midline shift	Categorical	Intoxicated EToH time of injury	Categorical		
Comment on size of bleed		Seizures before arrival ED	Categorical		
Additional injuries	Categorical	Vomiting before arrival ED	Categorical		
Sats on arrival ED	Continuous	A pedestrian or cyclist struck by a motor vehicle	Categorical		
		A fall from height of > 1 m or 5 stairs	Categorical		

Comorbidities will be measured using a trauma-modified Charlson Comorbidity Index. Brain injury severity, as shown on CT scan, will be stratified using the Marshall Classification, which will be calculated from Abbreviated Injury Severity (AIS) codes for TBI using the method described by Lesko et al. [16, 17] The Charlson Comorbidity Index, AIS and Marshall Classification are internationally validated prognostic scoring systems [18, 19]. Frailty will be assessed using the clinical frailty scale described by Rockwood et al. [20].

### Data collection

#### Screening

A database of all emergency department CT brain requests and reports for patients aged 16 and over between 2007 and 2017 will be generated at the two sites from the electronic requesting and reporting system. This will be screened to identify potentially eligible patients with CT requests related to head injury and CT scans with reported abnormalities related to TBI or intra-cranial haematomas (Fig. 2). Patients identified in this way will be matched to electronic ED case notes, reports and discharge summaries to identify the subset of patients potentially admitted with an initial GCS13–15.

**Fig. 2 Fig2:**
[figure not shown]
Population screening and selection

#### Data extraction

The full case records of patients identified through screening as potentially meeting the inclusion criteria will be retrieved (Fig. 2). In patients who are confirmed to meet the inclusion criteria, all a priori candidate prognostic factors will be extracted from the case records. Demographic information will be extracted from data recorded at the time of presentation to the ED following head injury. Comorbidities, frailty and pre-injury medication use will be extracted from that recorded in the ED attendance and subsequent inpatient hospital admission documentation. Comorbidities recorded in the inpatient notes up to 1 year prior to the presentation following head trauma will be included in accordance with the method of data collection in a recent update of the Charlson Comorbidity Index [19].

The full inpatient records will be interrogated for evidence of intervention or clinical deterioration that would meet the composite outcome measure. Recorded patient ED and hospital admissions after discharge following the relevant admission for traumatic brain injury will be assessed for evidence of deterioration, intervention or readmission in the 30 days following the initial ED attendance.

Patients who were included in the national Trauma Audit and Research network (TARN) registry will be identified locally. Using an anonymous TARN study number, we will assess for any deaths recorded on the TARN registry within 30 days of admission.

